## Abstract

Type 2 Diabetes Mellitus (T2DM) remains a global health challenge, with increasing prevalence in the Middle East, especially in Qatar. The Primary Health Care Corporation (PHCC) is the main provider of diabetes care in the country. Systematic evaluation through clinical audits provides a structured approach to identify gaps and improve clinical practices. This study aims to evaluate the effectiveness of clinical audit-based interventions in enhancing the management and documentation of T2DM in PHCC settings in Qatar. This quasi-experimental study will be conducted in three phases: pre-intervention, intervention, and post-intervention. In the pre-intervention phase, a cross-sectional situational analysis will be conducted across 31 PHCC health centers by reviewing 450 randomly selected patient records of adults diagnosed with T2DM. A baseline analysis will identify gaps in adherence to evidence-based diabetes care guidelines. The intervention phase will introduce specific quality enhancement strategies, which will encompass staff training, the distribution of guidelines, the engagement of audit champions, and various additional initiatives. Post-intervention, another 450 records will be audited to assess improvement. Additionally, 60 patients will be surveyed via telephone before and after the intervention to assess perceptions of care. The ICAE-DM CARE study aims to evaluate enhancements in clinical documentation, evaluation, and assessment of co-morbidities among patients with diabetes, alongside screening practices, adherence to evidence-based management protocols, and patient satisfaction levels. The findings will facilitate the institutionalization of audit-driven quality improvement initiatives within primary care settings. By providing robust evidence for integrating clinical audits into routine diabetes management, the study seeks to improve patient outcomes and support the objectives outlined in Qatar’s National Health Strategy.

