### Sample selection

A stratified simple random sampling method will be employed to select representative samples for both the cross-sectional and cohort components of the study. For the cross-sectional analysis, a total of 450 patient records will be randomly selected from the medical records department across 31 health centers. This sample size was calculated based on a 5% margin of error, a 95% confidence interval, and an assumed response distribution of 50%, with an additional allowance for potential non-responses. The selection will take place at two different time points: baseline and post-intervention, with 450 cases reviewed at each stage to facilitate a comparative analysis of diabetes-related encounters over the preceding three months.

For the patient satisfaction component, a subset of 60 patients will be randomly selected at each time baseline and post-intervention—from the larger cohort. These patients will be contacted by telephone to complete satisfaction surveys, offering qualitative insights into their perceptions of care. The randomization process will be independently applied at both time points to ensure comparability and minimize selection bias. A sample size of 60 patients per time point is considered sufficient to balance feasibility with the need for meaningful analysis of patient satisfaction trends. This approach ensures the robustness and reliability of findings and supports a comprehensive evaluation of both clinical outcomes and patient perspectives throughout the intervention period.

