### Patient satisfaction survey

A structured telephone-based patient satisfaction survey will be conducted with a sub-sample of patients. The survey is based on key performance indicators (KPIs) aligned with PHCC clinical practice guidelines for diabetes management. This tool was developed and validated by the Department of Clinical Effectiveness to ensure relevance and reliability in measuring patient experience.

Survey data will be recorded using a secure Excel spreadsheet preformatted with all measurement parameters. *(see*
Table 2
*for Patient Satisfaction Questionnaire).*

**Table 2 pone.0313664.t002:** Patient Satisfaction Survey Indicators.

Question	Indicator
Q1	Did your doctor inquire about and discuss diabetes-related signs and symptoms?
Q2	Did your doctor request any new blood tests or referrals?
Q3	Did your doctor explain how to monitor blood sugar and what to do in case of high/low readings?
Q4	Did your doctor provide advice about diet and physical activity?
Q5	Did your doctor set an HbA1c goal and discuss your treatment plan?
Q6	Overall, are you satisfied with the care provided during your visit?

Source: PHCC clinical practice guideline for the management of Type 2 Diabetes.

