### Analytical plan

Data will be extracted from the electronic health record system at two separate points: one time at a point before the intervention and the other time at a point after the implementation of the intervention. Excel will be used to collect and organize the data. PivotTables will be used to determine the frequency of cases across variables. Excel will be further used to produce histograms and other figures.

Study outcome variables will be assessed using independent tests like Chi square or t test to compare between the two groups. For satisfaction, we will do it frequently by percentage P=(F/T) *100.

The statistical analysis will be performed using STATA 15.1 (College Station, TX, USA). A Wilcoxon sign rank test will be used to find the mean difference between the pre- and post-assessment. P < 0.05 will be considered statistically significant. A logical model of protocol presented in Fig 2.

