## Conclusion

This comprehensive study underscores the pivotal role of clinical audits in enhancing the quality of diabetes care within primary healthcare settings. By systematically assessing current practices, identifying care gaps, and implementing targeted multidisciplinary interventions, the ICAE-DM CARE study aims to demonstrate measurable improvements in clinical management, documentation, and patient satisfaction among adults with T2DM. The pre- and post-intervention design provides robust evidence on the effectiveness of structured quality improvement initiatives, highlighting their potential to foster sustainable changes and elevate standards of care. Findings from this study will offer valuable insights into the integration of audit cycles into routine practice, emphasizing the importance of collaborative efforts, continuous monitoring, and data-driven strategies. Ultimately, this approach can serve as a scalable model for primary care facilities worldwide seeking to optimize chronic disease management and improve patient outcomes through systematic quality assurance processes.

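### Satisfaction is given only a percentage, with no between-round difference or interval and no named outcome item, although showing improvement in it is a stated aim

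*Protocol article*

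**What the plan says.** The aim is comparative. According to the Conclusion, the study "aims to demonstrate measurable improvements in clinical management, documentation, and patient satisfaction among adults with T2DM". The Abstract and the section on intervention and follow-up also promise an assessment of change in satisfaction or patient experience.

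The Analytical plan first assigns chi-square or t tests to the study outcome variables. It then turns to satisfaction separately: "For satisfaction, we will do it frequently by percentage P=(F/T) *100". A later paragraph adds a Wilcoxon signed rank test for the pre/post comparison, without naming the outcome it serves, and a 0.05 significance level.

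Under Sample selection, 60 patients are taken at each time point and "The randomization process will be independently applied at both time points". That number is "considered sufficient to balance feasibility with the need for meaningful analysis of patient satisfaction trends"; no precision or power is given. The Abstract says that "60 patients will be surveyed via telephone before and after the intervention to assess perceptions of care", and the study design section calls the survey component a cohort.

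Table 2 lists six items under a satisfaction title. Q6 reads "Overall, are you satisfied with the care provided during your visit". The other five ask about the doctor's actions, for example "Did your doctor request any new blood tests or referrals".

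**The concern.** The article fixes a method for satisfaction that describes each round, while the aim is to show a change between rounds. Two percentages set side by side, without the uncertainty of their difference, invite a chance movement of several points to be read as improvement.

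The label adds a second risk. The action plan is directed at processes such as goal setting, referral and counselling, and Q1 to Q5 ask about processes of this kind. If those items count as satisfaction, the intervention could raise the reported figure without any patient being more satisfied.

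**Working it through.** **1. The plan's own figures.** The 60 has no inputs behind it and cannot be reproduced. The record sample does have inputs: 1.96² × 0.5 × 0.5 / 0.05² = 384.1, so 385 records, and 450 follows with a non-response allowance of about 14.4% (385 / 450 = 0.856), a figure the article does not give. So precision was considered for the records but is not stated for the survey. For comparison, one survey percentage at 50% has a half-width of 1.96 × √(0.25/60) = 12.7 points, against the 5 points planned for the records.

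**2. Which test fits.** A signed rank test needs two measurements on the same patient. Independent draws at each round plan for no such pairs. The percentage formula is not a comparison. That leaves the general chi-square sentence, which the article does not connect to satisfaction.

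**3. Precision and power with 60 per round.** Inputs: n = 60 per round (Sample selection), independent groups, two-sided 0.05 (sidedness assumed), all 60 interviews completed, simple random sampling. No baseline rate is given, so 50% to 90% is assumed.

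- Half-width of the difference: 1.96 × √(2p(1−p)/60). At 50%: 1.96 × 0.0913 = 0.179. At 80%: 1.96 × 0.0730 = 0.143.
- Chance rise: the exact binomial probability that round two exceeds round one by at least 6 of 60 patients when nothing has changed.
- Power, with p̄ the mean of p1 and p2: Φ{[(p2−p1) − 1.96√(2p̄(1−p̄)/60)] / √([p1(1−p1)+p2(1−p2)]/60)}. For 70% to 80%: (0.10 − 1.96 × 0.0791) / 0.0785 = −0.70, giving 24%.

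| Assumed rate | Half-width of difference (points) | Chance rise of 10+ points, no true change | Power for a 10-point rise | Smallest rise with 80% power (points) |
|---|---|---|---|---|
| 50% | 17.9 | 15.8% | 19% | 24.5 |
| 60% | 17.5 | 15.3% | 21% | 22.9 |
| 70% | 16.4 | 13.6% | 24% | 20.2 |
| 80% | 14.3 | 10.4% | 33% | 16.4 |
| 90% | 10.7 | 4.6% | not calculated | not calculated |

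An example: observed 80% then 90% gives a difference of 10 points with a half-width of 1.96 × √((0.16+0.09)/60) = 12.7 points, so an interval from about −2.7 to 22.7.

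**4. What the percentage could be a percentage of.** F and T are undefined. If T were all answers, it would be 6 × 60 = 360 per round, with Q6 supplying one sixth. As an illustration, a 12-point rise in each of Q1 to Q5 with Q6 unchanged would lift the pooled figure by 5 × 12 / 6 = 10 points. The article does not say that items are pooled, nor that they are not.

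**5. Overlap with the chart audit.** Q4 (diet and activity advice) corresponds to Criterion 5 in Table 1, and Q5 (HbA1c goal) overlaps Criterion 3.

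**The case against.** The strongest reply is that the quoted sentence only says how satisfaction is summarised. The preceding sentence applies independent-group tests to outcome variables, and the follow-up section promises direct comparison of the rounds. A reader might infer that the article rules out any test and leaves the percentages to be compared by eye; it does not say so. What stands is narrower: satisfaction is set apart with a percentage, and no comparison is tied to it.

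Other tempting readings also go too far:

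- **That no change in satisfaction could be told from noise.** Two percentages with known denominators allow an interval, and large rises would be detectable.
- **That the six items will be pooled, or that a rise in Q1 to Q5 will be reported as satisfaction.** No section states this. The survey is also described as a validated measure of patient experience, and asking what the doctor did suits that purpose. The weakness lies in the label and the unnamed outcome.
- **That satisfaction is one of the two domains on which the audit is judged.** The section on evaluation of audit impact names care delivery and documentation. Satisfaction is a stated aim, measured in a sub-sample.
- **That Q2 has no favourable direction.** This depends on the population. The record review focuses on newly diagnosed patients, for whom Table 1 expects tests and referrals; the study population section also admits follow-up patients.

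Item scoring and the choice of interval are often left to a fuller document. That answers a complaint about missing detail. It does not answer the point that the method actually printed does not serve the printed aim.

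**Conclusion.** The point holds as a mismatch between method and aim. Of the analyses the article names, the one given to satisfaction is descriptive, the paired test does not fit independent draws, and the independent-group test is not linked to satisfaction. Q6, the only item that asks about satisfaction, is not identified as the outcome.

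In size, a movement of about 10 points cannot be separated from chance at any of the assumed rates, and a true rise of that size has 19% to 33% power from baselines of 50% to 80%. These figures rest on the assumed rates and on two independent groups. If the same 60 patients were surveyed twice, as the Abstract and the cohort label can be read, the figures would not apply and a paired analysis would be needed.

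**What to change.** 1. Reconcile the cohort label and the Abstract's wording with the independent sampling under Sample selection, and state which outcome, if any, the signed rank test serves.
2. With independent samples confirmed, name Q6 as the satisfaction outcome, define F and T for it, and report the between-round difference with a 95% CI for two independent proportions, for example Newcombe's.
3. Report Q1 to Q5 item by item as patient-reported care processes, beside the matching chart criterion where there is one (Q4 with Criterion 5, Q5 with Criterion 3).
4. Replace the statement that 60 is sufficient with the precision it gives under stated assumed rates: about ±18 points at 50%, ±14 at 80% and ±11 at 90%.

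The cost is wording and one routine interval. The questionnaire and sample size stay as they are. The downside is a more modest claim about satisfaction.

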## Methodology

### Study design and population

This study employs a mixed-methods approach, comprising a quasi-experimental design for cross-sectional data analysis and a cohort design for patient satisfaction surveys. The research will be conducted over a two-year period, from July 2025 to July 2027. Data will be extracted from the Electronic Medical Records (EMR) system of the Primary Health Care Corporation (PHCC), focusing on patients diagnosed with type 2 diabetes mellitus.

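### A paired Wilcoxon signed-rank test is planned for two independently drawn samples, so its p-value depends on row order; the survey is also mislabelled a cohort

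*Protocol article*

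**What the plan says.** - **Test, Analytical plan:** "A Wilcoxon sign rank test will be used to find the mean difference between the pre- and post-assessment", with "P < 0.05 will be considered statistically significant". Whether the test is one- or two-sided is not stated.
- **Other tests, same section:** "Study outcome variables will be assessed using independent tests like Chi square or t test to compare between the two groups". No rule says which outcome gets the independent tests and which the signed-rank test.
- **Sampling, Sample selection:** records are reviewed in two waves, "with 450 cases reviewed at each stage to facilitate a comparative analysis". For the survey, "a subset of 60 patients will be randomly selected at each time baseline and post-intervention". For both, "The randomization process will be independently applied at both time points to ensure comparability and minimize selection bias".
- **Abstract:** "Post-intervention, another 450 records will be audited to assess improvement". It also describes 60 patients telephoned before and after the intervention, which could be read as the same people.
- **Design label, Study design and population:** "a cohort design for patient satisfaction surveys".

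The article does not mention re-contacting patients, linking records or matching the two waves.

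**The concern.** The signed-rank test works on within-unit differences. When each wave is a fresh random draw, row 1 before and row 1 after belong to different people, and their difference measures nothing. A few patients may be drawn twice by chance, but that does not supply a full set of pairs.

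The text conflicts in two further ways. Paired and unpaired tests are both named for the pre/post contrast with no allocation between them. The survey is a cohort in one section and is independently redrawn in another. If the cohort label is right, the independent tests are wrong for the survey. If the redraw is right, the signed-rank test is wrong. The record audit has no paired reading at all.

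The signed-rank test also does not estimate a mean difference. The Table 2 questions and most Table 1 criteria read as yes/no items (the response scale is not given, so this is an inference). For such items the natural summary is a difference in proportions.

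The comparison of the two waves is the study's only test of whether the audit cycle worked, so the choice of test decides what the study can report.

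**Working it through.** **1. The plan's own figure.** The sample size is a single-proportion precision calculation: n = 1.96² × 0.25 / 0.05² = 384.1, so 385. Reaching 450 implies a non-response allowance of 1 − 385/450 = 14.4%; the article does not state the allowance. So 450 is reproducible, and the correction below changes neither 450 nor 60.

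**2. Why row order matters.** For a 0/1 item, drop the zero differences. Let b be the rows going no→yes and c the rows going yes→no. The signed-rank statistic (normal approximation) becomes z = (b − c)/√(b + c), which is McNemar's test without correction. The margins fix b − c. The number of discordant rows, b + c, depends only on how the two lists are lined up.

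**3. Survey size, assumed counts 30/60 before and 40/60 after, two-sided.**
- Two-sample chi-square without continuity correction: 3.43, p = 0.064, in any row order.
- Signed-rank: b − c = 10 always, so z = 10/√(10 + 2c).

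| Row alignment | b + c | z | p |
|---|---|---|---|
| Both files sorted by answer | 10 | 3.16 | 0.0016 |
| Largest b + c still below 0.05 | 26 | 1.961 | 0.0499 |
| Average random order | 30 | 1.83 | 0.068 |
| Files sorted in opposite directions | 50 | 1.41 | 0.157 |

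In random order c is hypergeometric (30 before-yes rows matched against 20 after-no rows out of 60), and p < 0.05 requires c ≤ 8. That has probability 0.206. Simulation agrees: over 2,000 random orders p ran from 0.018 to 0.123, with 21% below 0.05. The central 95% of orders has c from 6 to 14, giving p from 0.033 to 0.105.

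A second assumed case, 36/60 vs 46/60, has chi-square p = 0.0497, and 52% of 10,000 random orders gave a signed-rank p below 0.05.

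**4. Audit size, assumed counts 225/450 vs 252/450.** Chi-square p = 0.071. Over random orders the central 95% of signed-rank p-values is 0.059 to 0.085, and fewer than 0.1% of orders fall below 0.05. If both files are sorted by the item, p = 2 × 10⁻⁷; sorted in opposite directions, p = 0.19.

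**5. Type I error with no true change.**
- Random row order: 5.2% (60 per wave, 60% yes in both waves).
- Both files sorted by the item: c = 0, so z = √|d|, where d is the difference in yes counts. The test rejects when |d| ≥ 4. With 50% yes, the SD of d is √(2 × 60 × 0.25) = 5.48 at n = 60 and √(2 × 450 × 0.25) = 15 at n = 450. P(|d| ≥ 4) is then 52% and 82% (81% in the 4,000-replicate simulation). At 90% yes it is about 28% and 70%.

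**The case against.** The best defence has four parts.

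1. **A suitable test is already named.** The independent chi-square or t test is attached to the study outcome variables, so the signed-rank sentence may be meant only for the survey. With the cohort label and the abstract's wording, a paired analysis of the same 60 people would be coherent. *This stands in part:* the charge is an unresolved conflict between two test families, not reliance on the wrong one alone. But Sample selection is the more specific text and redraws the survey patients, so one passage has to change on either reading.
2. **The effect is mild where it matters most.** In random row order at 450 per wave, the signed-rank test nearly agrees with chi-square, and type I error stays near 5% even at 60. *This stands.* The ordinary harm is a p-value that cannot be reproduced, mainly in the survey.
3. **The sorted-file error rates are a worst case.** Both files must be sorted by the item being tested, and one sheet cannot in general be sorted by every criterion at once. *This stands.* The rates bound what Excel sorting could do to an item; they do not predict what will happen.
4. **A centre-level analysis would be valid.** Before/after differences across the 31 health centres are true pairs. *True, but the article describes no such analysis*, and 60 survey patients over 31 centres is about two per centre (60/31 = 1.9).

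None of this supplies patient-level pairs, and naming an unsuitable test is a misstatement rather than a detail left to a fuller document.

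**Conclusion.** The concern holds and must be fixed. As sampled, neither the audit nor the survey yields patient-level pairs, so a patient-level signed-rank test has no valid use here. The section names incompatible tests for the pre/post contrast, and the cohort label contradicts the sampling text.

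The size depends on row order. For a borderline survey item (30/60 vs 40/60), one data set gives p from 0.018 to 0.123 over 2,000 random orders and 0.0016 if sorted, against a single chi-square p of 0.064. For the 450-record audit the spread in random order is small. Type I error is about 5% in random order and, as a worst case, 52% (n = 60) or about 81–82% (n = 450) if both files are sorted by the item.

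These figures assume yes/no scoring, illustrative counts, two-sided testing and, for the worst-case rates, a 50% yes proportion. The contradiction in the text needs none of these assumptions.

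**What to change.** 1. Delete the signed-rank sentence from the Analytical plan.
2. For each Table 1 criterion and each survey item, compare the waves by a difference in proportions with a 95% confidence interval and a two-sample test. Use a rank-sum or t test only if a score is formed. Allowing for health centre, given sampling across 31 centres, would be a sensible refinement.
3. In Study design and population, describe the survey as repeated independent cross-sections, and align the abstract's wording.
4. If the sponsor does intend to re-interview the same 60 people, say so instead: remove the independent redraw for the survey, record a linking identifier, and use McNemar's test for yes/no items (signed-rank only for a paired score). The record audit stays unpaired.
5. Under the independent draws, keep a signed-rank test only if it is specified on the 31 centre-level before/after differences.

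The cost is a wording change to the analysis and design paragraphs, with no extra data and no change to 450 or 60 per wave. The choice between items 3 and 4 should be made before the baseline interviews, because a link that was not recorded then may not be recoverable.
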